#### Exploratory endpoints

2.3.5

Some optional endpoints in the treatment of patients with ALK+ NSCLC are defined: 1) Predictive value of response to treatment (i.e. PFS) by next-generation sequencing (NGS) using AVENIO ctDNA test, with emphasis on acquired resistance mechanisms by the following subgroup of response: a) ctDNA profiles associated with primary resistance PD within 6 months); b) ctDNA profiles associated with acquired resistance (PD 6-24 months); c) ctDNA profiles associated with continuing response of 2 years and more; 2) Concordance of molecular profile between tumor biopsy NGS and ctDNA at baseline. As well as at PD, after performing a re-biopsy as standard of care; 3) Correlation with average daily exposure and reduction in ctDNA levels. To obtain DNA from cell free plasma, blood will be withdrawn at baseline in three Streck^®^ tubes (Streck Inc, Omaha, NE, USA) and one EDTA tube (Vacutainer) to process the buffy coat (consisting of peripheral blood mononuclear cells), to identify tumor-specific mutations using NGS analysis and exclude variants associated with germ-line, clonal hematopoiesis and technical artefacts. Each subsequent cycle, two Streck tubes will be collected. CtDNA will be analyzed using the Avenio ctDNA Expanded covering 77 clinical-relevant markers (19). There is ample experience using this Avenio ctDNA Expanded Kit of large plasma samples (20, 21).

Furthermore, additional data regarding the effects of alectinib on weight gain will be collected. These exploratory endpoints are defined as follows: 4) Parameters such as body weight, body surface area and smoking; 5) Changes in body composition measured on CT-thorax/abdomen, including subcutaneous and visceral adipose tissue measurements, using specialized software; 6) Measurements of appetite and satiety hormones and their relationship to alectinib therapy related weight gain.

### Data analysis

2.4

Survival endpoints will be analyzed using Kaplan-Meier curves and differences between groups will be tested using the stratified log rank test. The HR and its corresponding 95% CI from a stratified Cox model will be estimated. The median survival will be presented by arm along with 95% confidence intervals using the Brookmeyer and Crowley method. A p-value < 0.05 will be deemed statistically significant.

The effect of biomarkers in the secondary and exploratory study parameters (such as sequencing profile by AVENIO of biopsy) will be explored by correlating the changes in a marker to any outcome (such as OS). This will be performed by crosstabs, t-tests, Mann-Whitney U tests, and Spearman’s rank correlations, depending on the distribution of the data.

ORR will be calculated by arm with exact 95% CI. For comparing response rates in the two-treatment arms accounting for randomization stratification factors, the Cochran-Mantel-Haenszel test will be used at a two-sided 5% level of significance.

For treatment-emergent AEs (i.e., those starting or worsening during the period on treatment) summary tables will be provided by treatment group. Worst-grade AEs will be summarized by system organ class and preferred term, severity (by CTCAE v5.0 criteria) and relation to study treatment. Serious adverse events will be listed. Statistical analyses will be specified in the Statistical Analysis Plan.

Comparative cost-effectiveness analysis will be performed using a health-state transition model, to compare costs and effectiveness between the group treated with TDM-guided dosing and the fixed dosing group. The comparative cost-effectiveness analysis will be performed from both a healthcare and societal perspective, with a lifetime horizon, according to the Dutch guidelines for cost-effectiveness analyses (22).

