### Study design

2.2

The ADAPT ALEC trial is an international, multicenter, phase IV, RCT comparing TDM-guided dosing to standard dosing of alectinib. Initially the trial will be open at seven study sites in the Netherlands, after which international sites will follow. The study design is displayed in **Figure 1**. Patients will be centrally randomized according to the minimization method in a 1:1 ratio, stratified by prior treatment with other ALK inhibitors and presence of brain metastases, using the online randomization tool ALEA v.18.3 (FormsVision BV, Abcoude, The Netherlands). The trial will compare, in the subgroup of patients with alectinib plasma concentration C_min,SS_ < 435 ng/mL at any time point, those receiving dose-adjusted alectinib based on TDM (arm A) with those receiving standard treatment with fixed dose alectinib (arm B).

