#### Sample size calculation

2.3.2

It is expected that 48% of the patients treated with alectinib in our study will be underdosed (i.e. C_min_ < 435 ng/mL at a certain timepoint) based on the dataset of Groenland et al. (13). The observed mPFS for these patients was 12.6 months (95% confidence interval (CI): 9.2 months – not yet reached), which will serve as the assumed median in the subgroup with low exposure in the fixed-dosing group (arm B). The mPFS in the patients with C_min_ ≥ 435 ng/mL had not yet been reached (95% CI: 19.8 months – not yet reached) at the time of analysis, but the HR for the group with C_min_ < 435 ng/mL versus C_min_ ≥ 435 ng/mL was estimated as 2.5 (13). We expect that TDM-guided dosing can improve PFS in 67% of patients with a low exposure, to the extent that they obtain a similar outcome as patients with C_min_ ≥ 435 ng/mL. In this group, a HR (fixed versus TDM-guided dosing) of 2.5 is assumed. In the remaining 33% of patients, TDM-guided dose increases are expected not to be feasible due to toxicity or treatment discontinuation as a consequence of progressive disease (PD), so a HR equal to one is assumed for this subgroup. Altogether, this would result in an expected HR (fixed versus TDM-guided) of 2.0. With 67 events, a power of 80% will be obtained to detect this HR of 2 using the log-rank test and assuming a two-sided significance level of 5%. This translates into an improvement in mPFS from 12.6 months without using TDM-guided dosing to 25.2 months using TDM-guided dosing. Assuming an uniform patient accrual during 48 months and 12 months follow-up after inclusion of the last patient (total study duration of 60 months), 94 patients (47 per group) with C_min _< 435 ng/mL will need to be included for the primary analysis. Since 48% of the patients in the study are expected to have C_min _< 435 ng/mL at a certain timepoint, 196 patients will need to be recruited (13). Dropouts are expected to be kept to a minimum and it does occur, it is expected to be in the first 12 weeks, when substitution is still allowed. Dropouts are therefore not taken into account.

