#### Primary outcome

2.3.3

The primary outcome, based on our aim to improve efficacy of alectinib treatment, is mPFS in the TDM-guided dosing arm for the C_min,SS _< 435 ng/mL subgroup, compared to this subgroup in the fixed dosing arm (standard care). PFS will be calculated as time from start of treatment to PD, death of any cause, whichever occurs first. Patients who do not progress, die, or are lost to follow-up, will be censored at their last available date. PD is defined according RECIST v1.1 and will be based on assessment using CT scans (thorax/abdomen) and MRI of the brain. In case of oligoprogression alectinib may be continued conform standard of care, but the date of oligoprogression (i.e. PD) will be used in PFS calculation. The CT scans will be performed every 8 weeks in the 1^st^ year and every 12 weeks from the 2^nd^ year onwards. The MRI of the brain will be performed every 16 weeks in the 1^st^ year if there is presence of asymptomatic brain metastases at screening and every 24 weeks from the 2^nd^ year onwards. If no brain metastases are found at screening, an MRI of the brain will be performed every 12 months (**Supplemental Table 1**).

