## Discussion

3

The purpose of ADAPT ALEC is to investigate in an RCT whether patients with ALK+ NSCLC would achieve better treatment outcomes when using personalized dosing.

The proposed TDM target of 435 ng/mL, was based on the dose-finding study, where patients with exposure in the lowest tertile had less reduction in tumor size compared with the upper two tertiles (C_min,SS_ ≥ 435 ng/mL) (12, 13). The manufacturer of alectinib identified baseline tumor size as only significant covariate for best overall response, while combined average concentration of alectinib and its metabolite M4 was not significantly correlated with best overall response (12). In research of Morcos et al. an exposure-response analysis of alectinib was performed in 207 crizotinib- resistant patients with ALK+ NSCLC. No significant relationship was found between OS and trough levels (14). Given the observational nature of these findings in exposure-response analyses, which are not consistent with each other, a prospective study is necessary to evaluate the hypothesis that TDM of alectinib would result in better treatment outcomes.

Notably, this type of research has not been performed often, and when it was designed it was not always proven successful, as illustrated by the trial of Gotta et al. and the aborted SARC019 trial which tested TDM of kinase inhibitors (25, 26). Gotta et al. provided suggestions to consider when designing such RCTs in the future, which we took into consideration when designing this trial protocol. One of the suggestions was differentiating between efficacy and safety outcomes, which is captured by a primary endpoint based on efficacy, and a secondary endpoint on toxicity (in relation to plasma trough levels of alectinib). Additionally, investigating reasons for prescribers’ non-adherence to dosage recommendations is captured by formulating the physician adherence as a secondary endpoint. The authors also recommended restricting the inclusion to treatment naïve patients. In the ADAPT ALEC protocol, stratification will be applied in randomization for first- and second-line treatment. Another issue raised was that TDM could encourage drug discontinuation in patients intolerant despite acceptable plasma trough concentrations. In this protocol, this is not specifically defined, in case of intolerance it is allowed to reduce the dose, which will happen regardless of plasma levels, before switching therapy, which is in accordance with regular care.

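### The PFS and ORR analyses use only the two stratification factors; pre-specifying baseline tumour size is a cheap efficiency improvement, though its value for PFS must be assumed

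*Protocol article*

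**What the plan says.** The Data analysis section of the protocol article names the efficacy methods. For time-to-event endpoints, "differences between groups will be tested using the stratified log rank test", and "The HR and its corresponding 95% CI from a stratified Cox model will be estimated". For ORR, "accounting for randomization stratification factors, the Cochran-Mantel-Haenszel test will be used at a two-sided 5% level of significance". The Study design section gives the factors: randomisation is "stratified by prior treatment with other ALK inhibitors and presence of brain metastases". No other baseline covariate is named, and further detail is left to the SAP.

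The Discussion reports, from the manufacturer's exposure-response work, that "The manufacturer of alectinib identified baseline tumor size as only significant covariate for best overall response". It does not say whether tumour size predicts PFS or OS. The Primary outcome section states that "PD is defined according RECIST v1.1 and will be based on assessment using CT scans (thorax/abdomen) and MRI of the brain". The article does not say in so many words that a baseline sum of target-lesion diameters is recorded for every patient, but assessment by RECIST v1.1 implies that one is taken where there is measurable disease.

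**The concern.** The document itself names a baseline variable that predicts response to this drug, and the planned comparisons do not use it. For ORR, a secondary endpoint, the cited evidence bears directly on the comparison. For PFS a link is plausible, since progression is judged by the same criteria, but the documents do not establish it.

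Precision matters more than usual here. The primary comparison uses about 94 of 196 patients, with 67 events and no allowance for dropout. The Discussion concedes that an HR of 2.0 is a demanding target, that a smaller effect would need more events than is feasible, and that there is no margin for non-evaluable patients. If patients cannot be added, using baseline information already collected is one of the few remaining ways to gain power.

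**Working it through.** **Step 1. Reproduce the planned design.** The Sample size calculation section states: "With 67 events, a power of 80% will be obtained to detect this HR of 2 using the log-rank test", two-sided 5%, medians 12.6 and 25.2 months, 48 months of uniform accrual plus 12 months of follow-up, 94 patients analysed, 48% with low exposure, 196 recruited.

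- Events (Schoenfeld, 1:1): 4 × (1.960 + 0.842)² / (ln 2)² = 65.3, so 66, against 67 stated. Freedman's formula gives 71.
- Power at 67 events: Φ(√67 / 2 × ln 2 − 1.960) = 81.0%.
- Event probability per arm, exponential PFS with rate λ = ln 2 / median: 1 − (e^(−12λ) − e^(−60λ)) / (48λ) = 0.818 (fixed dosing) and 0.601 (TDM), mean 0.710.
- Patients: 67 / 0.710 = 94.4; recruited: 94 / 0.48 = 195.8.

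The plan's figures reproduce.

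**Step 2. Effect of adding one baseline covariate on PFS power.** The setting is 94 patients, the accrual and follow-up above, four strata and 4,000 simulated trials per row. The two factors were given assumed prevalences of 40% and 20% and no effect on the hazard. Tumour size enters as a standardised continuous covariate; its HR per SD is an assumption, so a range is shown. The conditional HR was calibrated so that the HR ignoring tumour size stays at 2.0. The comparison is the stratified log-rank test against the Wald test for treatment in a stratified Cox model with the covariate.

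| Assumed PFS HR per SD | Conditional treatment HR | Stratified log-rank | Adjusted Cox | Change (points) |
|---|---|---|---|---|
| 1.0 | 1.99 | 77.3% | 76.7% | −0.6 |
| 1.2 | 2.01 | 77.9% | 79.0% | +1.1 |
| 1.35 | 2.06 | 77.9% | 80.5% | +2.6 |
| 1.5 | 2.12 | 77.1% | 82.3% | +5.2 |
| 1.75 | 2.22 | 78.0% | 85.4% | +7.4 |
| 2.0 | 2.31 | 76.1% | 86.9% | +10.8 |

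The simulation error of each power value is about √(0.78 × 0.22 / 4000) = 0.7 points. The log-rank column lies a little below the 81.0% of Step 1. Splitting 94 patients into four strata and the optimism of Schoenfeld's approximation at this HR are the likely reasons. The change column compares the two tests on the same simulated trials.

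**Step 3. Type I error.** In 4,000 null trials at each HR per SD of 1.0, 1.5 and 2.0, the adjusted test rejected in 4.5%, 5.3% and 5.1%.

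**Step 4. Sensitivity to what is held fixed.** If the conditional HR is set to 2.0 instead (3,000 trials per setting), power goes from 78.8% to 78.6% at HR per SD 1.0, from 72.0% to 76.3% at 1.5, and from 61.1% to 75.1% at 2.0.

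**ORR.** No power figure is given: the documents state neither an expected ORR nor the strength of the tumour-size association.

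**The case against.** The strongest objection is that nothing here is wrong. The stratified log-rank test is valid, matches the randomisation factors and belongs to the family used for sizing. Model covariates are often left to a SAP, and the article defers to one. All of that stands, and it limits the point to a suggestion. What remains is that the article names specific tests and, elsewhere, a covariate that could improve them.

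Four stronger readings are tempting, and the documents do not support them.

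- A reader might infer that the plan's true power is 61% or 72%, from Step 4. Those values arise because fixing the conditional HR at 2.0 lets the unadjusted HR fall below 2.0. The plan states its HR of 2.0 for a log-rank test with no covariate, and with that HR held the planned test stays at 76% to 78% throughout. The planned medians do not rescue the stronger reading. In this model the ratio of medians equals the conditional HR, so the HR of 2.0 and the twofold medians cannot both hold once a covariate matters. The plan sizes on the HR.
- A reader might infer that adjustment is known to recover power for PFS. The cited evidence concerns best overall response only.
- A reader might infer that imbalance is likely because minimisation balanced 196 patients and not the 94. Tumour size is not a minimisation factor, so it is left to chance in both groups, and chance imbalance is already covered by the type I error of the test.
- A reader might infer that adjustment is free. It changes the target to a conditional effect, needs a functional form and a rule for patients without measurable disease, and loses about half a point of power if tumour size is not prognostic.

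**Conclusion.** The point holds as a low-cost efficiency improvement, of minor severity. The planned PFS and ORR tests are valid but leave unused the one baseline covariate that the article itself reports as significant for response. For ORR the rationale is direct, though its size cannot be computed from the documents. For PFS the power change runs from about −0.5 to +11 points. Where in that range the trial would lie depends wholly on an association that the documents do not give. The range also assumes a standardised, log-linear covariate, strata without effect on the hazard, and an HR of 2.0 when tumour size is ignored. Adjustment would not cure the definition of the primary subgroup by trough levels measured after randomisation; that is a separate matter.

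**What to change.** Before any comparison of outcomes by arm, write into the SAP:

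1. **PFS.** Add the log baseline sum of target-lesion diameters, plus an indicator for no measurable lesion, to the stratified Cox model that gives the HR. Report the unadjusted stratified log-rank result as well. State in advance which result carries the 5% test: the power changes tabulated above apply only if it is the adjusted one. If the log-rank test keeps that role, the adjusted model serves as a named supportive analysis.
2. **ORR.** Use a logistic model with arm, the two stratification factors, the same tumour-size term and the same indicator. Report the CMH result as well.
3. **Timing.** Tying the lock to the release of arm B trough results is too late. The article describes only those PK results as blinded, so outcomes by arm could be seen before then.

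The cost is analysis wording and a check that the baseline sum is captured in the eCRF; no extra patients or visits are implied. The HR and odds ratio become conditional on tumour size. The conditional HR need not equal the 2.0 used for sizing (2.12 at an assumed HR per SD of 1.5), so the report should say which effect is quoted.

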#### Secondary outcomes

2.3.4

There are ten secondary endpoints, defined as follows: 1) Feasibility and safety of TDM, measured as percentage of successful TDM interventions, in which successful is defined as target attainment with manageable toxicity; 2) ORR, defined as partial response or complete response (according to RECIST v1.1) percentage of the total treated population; 3) mOS, where OS is defined as time from randomization to death from any cause in the total population. Patients who do not die or are lost to follow-up will be censored at their last available date; 4) Intracranial PFS, defined as time from start of treatment to PD in the brain or death from any cause, whichever comes first. Patients not experiencing any of these events will be censored at their last available date; 5) Physician adherence to TDM advice, measured as the percentage of dose recommendations that are implemented by the treating physicians; 6) Patients’ medication adherence, estimated by pill counts of returned medication as well as a patient diary on drug intake; 7) Toxicity related to the plasma concentration and dose increases, defined as adverse events (AEs) in the subgroup with C_min,SS _< 435 ng/mL and all C_min,SS_ ≥ 435 ng/mL, and in patients who did and who did not receive a PK-guided dose increase; 8) QoL; this will be determined using the EORTC QLQ_LC13 as addition to the QLQ-C30 questionnaire, and the EQ-5D-5L questionnaire. 9) Cost-effectiveness, this will be determined from both a healthcare and a societal perspective. Costs associated with healthcare resource use in combination with Quality adjusted-life years will be used to determine an incremental cost-effectiveness ratio (ICER); 10) Alectinib-M4 concentrations, which will be measured in the alectinib plasma samples. For the endpoints regarding ORR, mOS, intracranial PFS, the comparison will be made between arm A and B, among patients who had a C_min,SS _< 435 ng/mL at any point during treatment. Feasibility and safety of TDM and physician adherence to TDM advice will only be evaluated in arm A. Patients medication adherence, toxicity, QoL, cost-effectiveness and alectinib-M4 concentrations will be evaluated in all patients.

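### Exploratory marker analyses against OS and PFS are assigned methods that cannot handle censoring, and the ctDNA response classes leave late-entering progression-free patients unclassified

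*Protocol article*

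**What the plan says.** The Data analysis section (2.4) of the protocol article treats survival endpoints and biomarkers in separate paragraphs.

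- **Survival endpoints:** "Survival endpoints will be analyzed using Kaplan-Meier curves and differences between groups will be tested using the stratified log rank test". A stratified Cox model gives the hazard ratio, and medians are shown by arm.
- **Biomarkers in secondary and exploratory parameters:** effects "will be explored by correlating the changes in a marker to any outcome (such as OS"). The methods follow at once: "This will be performed by crosstabs, t-tests, Mann-Whitney U tests, and" Spearman correlations, chosen "depending on the distribution of the data". Censoring is not a criterion.

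The Secondary outcomes section (2.3.4) makes OS a censored endpoint: "Patients who do not die or are lost to follow-up will be censored at their last available date". The Primary outcome section (2.3.3) censors PFS in the same way.

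The Exploratory endpoints section (2.3.5) takes PFS as the outcome that ctDNA should predict. It sorts patients into progression within 6 months, progression at 6 to 24 months, and a third class, "ctDNA profiles associated with continuing response of 2 years and more".

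The Sample size calculation (2.3.2) assumes uniform accrual over 48 months and "12 months follow-up after inclusion of the last patient".

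**The concern.** A t-test, a rank test or a Spearman correlation on observed times treats a patient alive at 14 months as if death had occurred at 14 months. The alternative is to drop that patient, which keeps only those who died within the study. Potential follow-up is set by calendar date of entry, so an observed time partly records when the patient enrolled.

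The biomarker sentence also speaks of change in a marker, which needs post-baseline samples. The article does not fix the window for that change. If the window is open-ended, patients followed longer contribute more of it.

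The ctDNA classes raise a related problem. A patient who enters late and progresses can always be classified. One who enters late and remains progression-free cannot.

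At stake is how far the trial's exploratory ctDNA findings can be relied on. The Discussion presents these as a contribution to prospective evidence on prediction of response.

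**Working it through.** **1. Reproducing the plan's own figures.** Inputs from section 2.3.2: HR 2, two-sided 5%, 80% power, 1:1 allocation, medians of 12.6 and 25.2 months, accrual A = 48 months, minimum follow-up F = 12 months, 48% with low exposure.

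Schoenfeld events: 4(1.960 + 0.842)²/(ln 2)² = 65.3, so 66. The plan states 67, which gives 81.0% power.

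Event probability for exponential times with median m and λ = ln 2/m:

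P(m) = 1 − [exp(−λF) − exp(−λ(A+F))]/(λA)

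P(12.6) = 0.818 and P(25.2) = 0.601, mean 0.710. Then 67/0.710 = 94.4 (stated 94) and 94/0.48 = 195.8 (stated 196). The accrual model used below is therefore the plan's own.

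**2. Censoring of OS.** The article gives no OS assumption. Its Introduction reports that median OS on alectinib was not reached at a median follow-up of 48.2 months in a first-line trial. Censored share 1 − P(m), by assumed median:

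| Assumed median OS (months) | Censored |
|---|---|
| 24 | 38% |
| 30 | 46% |
| 36 | 52% |
| 48 | 61% |
| 60 | 67% |
| 80 | 74% |

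Half are censored at a median of about 34 months, or about 39 months if accrual is extended by the permitted year.

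**3. Censoring of PFS.** The plan's HR of 2.5 puts the adequate-exposure median at 12.6 × 2.5 = 31.5 months, with P(31.5) = 0.526. Low-exposure TDM patients are a 67/33 mixture of the two outcomes: 0.67 × 0.526 + 0.33 × 0.818 = 0.622. Overall: 0.52 × 0.526 + 0.24 × 0.818 + 0.24 × 0.622 = 0.619 with events, so about 38% are censored. Using HR 2.0 in place of the mixture gives 0.614, or about 39%.

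**4. Effect of ignoring censoring on OS.** Simulation, 1000 runs per setting, with a binary baseline marker split 50:50 and observed times analysed as if complete:

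| Setting | Listed tests reject | Cox rejects |
|---|---|---|
| Marker HR 2, N = 196, median OS 48.2–57.4 | 52–62% | 82–86% |
| Marker HR 2, N = 94, same medians | 26–32% | 47–52% |
| No effect, no link to entry date, N = 196 | 4.5–4.9% | 4.1% |
| No effect, marker linked to entry date, N = 196 | 79–99.8% | about 5% |

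The last row assumes that mean entry dates of the two marker groups differ by 9.6 or 16 months, which is a strong link. Attenuation is also visible: at a median of 57.4 months and N = 196, a true mean difference of 59.0 months appears as 4.4 months in observed times. These runs use a baseline marker and do not model post-baseline change.

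**5. The ctDNA classes.** Patients entering in the last 24 − 12 = 12 months of accrual have under 24 months of potential follow-up: 12/48 = 25%, or 49 of 196. For follow-up uniform on 12 to 24 months, the progression-free share at cutoff is [exp(−12λ) − exp(−24λ)]/(12λ):

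- median 31.5: 0.675
- median 12.6: 0.378
- low-exposure TDM: 0.577 by the mixture, 0.612 by HR 2.0

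Weighted 0.52/0.24/0.24, this is 0.580 to 0.589, and 49 × that = 28 to 29 patients, or about 14.5% to 14.7% of 196. The modelled share progression-free at 24 months is about 49%. Among classifiable patients it would be 0.75 × 0.487/(1 − 0.145) = 0.43 by the mixture, or 0.75 × 0.495/(1 − 0.147) = 0.44 by HR 2.0.

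**The case against.** The best reply is that section 2.4 opens with a general rule for survival endpoints, and its reference to groups is not expressly limited to arms, so marker groups might fall under it. The section also defers detail to the SAP, which is not shown. Neither point removes the problem. The biomarker paragraph gives its own methods and names OS as its own example. That is a stated method which does not fit its outcome, not a detail left for later. A SAP that followed the text would inherit it.

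Other parts of the reply do stand. The text speaks of exploring, not of formal tests with a decision rule. The list suits much of what is planned, such as biopsy–ctDNA concordance, response, and exposure against ctDNA reduction. The article plans no specific survival comparison for M4 or for exposure, so the point does not extend to them beyond the general phrase about any outcome.

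Three stronger readings are tempting and are not supported:

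- **That the marker results will be biased or falsely positive.** Without a link between marker and follow-up length, the listed tests keep about 5% error and mainly lose power. Nothing in the article suggests that marker status drifts with enrolment. Selection through post-baseline change depends on a window the article does not fix, and a fixed early change would avoid it.
- **That all 49 late entrants are unclassifiable.** Those who progress are classified. Separate consent for exploratory outcomes makes 196 an upper bound.
- **That most OS times are certain to be censored.** This is inferred from a first-line benchmark, whereas second-line patients are also eligible and follow-up may be extended.

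**Conclusion.** The point holds for marker analyses against OS and PFS. The stated methods cannot handle outcomes that the article itself defines as censored.

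The censoring is substantial: about 61% to 74% of OS times at assumed medians of 48 to 80 months, over half for any median above about 34 months, and still 38% at 24 months. About 38% of PFS times are censored under the plan's hazards. These figures assume exponential times, 48 months of uniform accrual, 12 months of further follow-up and no dropout.

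The expected harm is attenuation and lost power: in the simulated case of a marker with HR 2 and 196 patients, 52% to 62% instead of 82% to 86%. False positives and selection bias are conditional risks.

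The ctDNA classes omit about 28 to 29 progression-free patients of at most 196, so progressors are moderately over-represented.

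A reader might infer that the trial's main conclusions are touched. They are not: the primary PFS analysis and the arm comparisons of OS and intracranial PFS use log-rank and Cox methods.

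**What to change.** Limit the change to marker analyses with OS or PFS as the outcome:

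- Use Cox regression, stratified by the randomization factors, with baseline markers as covariates. Use Kaplan-Meier curves and log-rank tests for marker categories.
- Enter on-treatment marker change as a time-dependent covariate, or measure it at a prespecified fixed landmark and count survival from that landmark among patients still at risk.
- Report the ctDNA response classes descriptively, in patients with at least 24 months of potential follow-up whether or not they progressed. Use the Cox analysis of PFS for all others as well.
- Keep crosstabs, t-tests, Mann-Whitney U tests and Spearman correlations for uncensored outcomes, such as response or ctDNA reduction against exposure.

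The cost is a few sentences in the SAP, with a matching clarification in the protocol. No new data, samples or visits are needed. The restriction reduces the set for the class description to about 75% of consenting patients (at most 147 of 196), but they remain in the Cox analysis.
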